## **6.2 Design**

Pragmatic, controlled, randomized, non-masked clinical trial with two parallel arms.

## **6.3 Measures to minimize or avoid bias**

### **6.3.1 Randomization**

Once the patients have received the study information and signed the corresponding informed consent, they will be randomized to usual care or to the intervention-self-monitoring and self-titration group (1:1 ratio) using a computerized randomization system. A randomization process with minimization will be carried out to preserve a balance between groups in variables considered key a priori by the research team. The minimization criteria will be: age, gender, SBP >160 mm HG, diabetes, cardiovascular disease (ischemic heart disease, heart failure, cardiomyopathy, and peripheral arterial disease), cerebrovascular accident (stroke), and chronic kidney disease.

### **6.3.2 Masking**

Due to the nature of the intervention, it is not feasible to blind the study for either the patients or the Research Family Physicians (MEFI), who are responsible for the patients. Likewise, the Collaborating Research Physicians (MIC), who will conduct the training interventions in the first year and collaborate with MEFI in follow-up visits, cannot be blinded

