## **6. DESIGN**

### **6.1 Outcome measures**

#### **6.1.1 Primary outcome measure**

Difference in mean systolic blood pressure, in mmHg. At 12 months of follow-up between the intervention and control groups, determined at physicians' practice with a validated automatic electronic sphygmomanometer.

At least 2 measurements should be taken in the sitting position, spaced 1-2 minutes apart, or an additional measurement if the first 2 are quite different. The average of the 2 measurements taken as valid will be considered as TA.

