#### **6.5 Patients follow-up**

The follow-up of the patients will be conducted by the MEFIs in line with routine clinical practice conditions. MEFIs will be responsible for patient selection and inclusion in the trial and will execute the training actions as outlined in point 6.4.

Additionally, the MIC team will reinforce the training and information actions specified by the MEFI and defined in point 6.4. However, it's important to note that the MIC team will not make clinical decisions or modify the management or recommendations of the MEFI. They will also handle data collection during the scheduled visits in the study, including the baseline visit and follow-up visits at 6 and 12 months, working in collaboration with the MEFI.

In the first 12 months of the study, the MIC team will conduct bi-monthly telephone reinforcement sessions. These sessions aim to contact patients in the intervention group with the goal of improving adherence to the intervention and addressing any potential concerns.

In the second year (passive or pragmatic follow-up), patient follow-up will be aligned as closely as possible with routine management in usual clinical practice. Therefore, the role of the MIC will be carried out by a nurse

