In turn, the Patient's Notebook for the control group will contain:

- First sheet: patient anonymization code, arm for taking blood pressure
- Information about the importance of hypertension and lifestyles
- Sheets for recording care contacts with your Health Center

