#### 8.5.3 Follow-up visits

- 6-Month Visit:
  - o Researchers will record data related to the variables of the follow-up visit (as outlined in **Table 2** of section 6.6). Data sources will include information provided by the patient, the Patient's Notebook, and the patient's electronic medical record.
  - o All patients, regardless of their group, will receive a 6-month follow-up appointment and will be informed that they will receive a reminder call beforehand. They should also bring their completed Patient's Notebook.
- 12-Month Visit:
  - o Researchers will collect data related to the variables of the follow-up visit (as detailed in **Table 2** of section 6.6), using information from the patient, the Patient's Notebook, and the electronic medical record.
  - o Patients, irrespective of their group, will be informed that they will continue with their group-specific trial instructions (self-monitoring/self-adjustment or usual care). Simultaneously, they will maintain their regular medical and nursing appointments. They will also be informed that they will receive a phone call for a final visit within a year and should bring their completed Patient's Notebook.
- 24-Month Visit:
  - o During this visit, a reduced set of outcome variables will be collected, including blood pressure, quality of life, and use of healthcare services (as outlined in **Table 2** of section 6.6).
  - o The purpose of this visit is to conduct secondary analyses after a period of passive follow-up. This aims to evaluate adherence to the intervention under conditions even closer to usual clinical practice. Additionally, results at 24 months will be obtained during this visit.

- During the period from months 12 to 24, MICs will not provide reminders, and nurses will carry out complementary assistance work alongside MEFIs for follow-up, adjustment plan renewals, etc.

If the patient does not attend the follow-up visits, the patient will be located by telephone to give a new date of visit or, in the event that he is not located or leaves the study, the date and the reason for it will be recorded. Any data collected from patients that does not appear in their clinical history will be included in it.

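### The 12-month systolic pressure (the primary outcome) is collected by unblinded staff at a visit where the Patient's Notebook can show the group, and the rule for which readings count leaves room for judgement

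*Protocol*

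**What the plan says.** The primary outcome (section 6.1.1) is the difference in mean systolic pressure, "At 12 months of follow-up between the intervention and control groups, determined at physicians' practice with a validated automatic electronic sphygmomanometer". All the following places are in the protocol.

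- **Who is unblinded.** Section 6.3.2 says that patients and MEFI cannot be masked because of the nature of the intervention. It adds the MIC, "who will conduct the training interventions in the first year and collaborate with MEFI in follow-up visits, cannot be blinded". It does not discuss outcome assessors.
- **What the MIC do.** They reinforce the training and make bi-monthly calls in the first year: "These sessions aim to contact patients in the intervention group with the goal of improving adherence to the intervention" (section 6.5). They also run group sessions for intervention patients (section 8.5.2).
- **Who collects the data.** The MIC again: "They will also handle data collection during the scheduled visits in the study, including the baseline visit and follow-up visits at 6 and 12 months", together with the MEFI (section 6.5; section 6.6 likewise makes both roles responsible). Section 8.5.3 says only that researchers collect the data. Blood pressure is among the 6- and 12-month items in Table 2.
- **What patients bring.** At the 6-month visit, patients in both groups are told about the next one: "They should also bring their completed Patient's Notebook". The Notebook is a named data source at the 12-month visit (section 8.5.3). Under section 8.5.1 the intervention version holds target figures, the self-adjustment plan and sheets for home pressures. The control version lists none of these.
- **How pressure is read.** A validated automatic device is used, with at least two seated readings 1 to 2 minutes apart and a further one if the first two are far apart. Section 6.1.1 and Table 3 average the two readings accepted as valid. The Table 2 footnote and Table 4 average the readings taken.

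**The concern.** Nobody assigned to collect the primary outcome is masked, and one of the two roles also has the task of making the intervention work. The reason given for not masking patients and treating physicians is sound. For the MIC, the reason is that they train patients and attend follow-up visits, which is a division of tasks and not a property of the intervention.

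The exposure is made worse by the order of events. No rule puts the pressure reading before the Notebook, so the measurer may see the target and the home values first. That person then decides whether two readings differ enough to need a third and, under section 6.1.1, which two are valid. No numeric threshold governs either decision.

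Every blood pressure outcome in the protocol is an office reading of this kind, so no masked or ambulatory measure could show whether the between-group difference had been shifted.

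**Working it through.** **1. Roles against knowledge of the group.**

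| Role | Knows the group? | Tied to the intervention? | Collects 12-month data? |
|---|---|---|---|
| MIC | Yes (6.3.2) | Trains, phones, runs group sessions (6.3.2, 6.5, 8.5.2) | Yes (6.5, 6.6) |
| MEFI | Yes (6.3.2; receives the allocation, 8.5.1) | Writes the self-adjustment plan (8.5.1) | Yes (6.5, 6.6) |

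Whichever role operates the cuff, the measurer is unblinded. The conclusion does not depend on which it is.

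**2. What the averaging discrepancy does.** Suppose a third reading is taken. Let m be the mean of the two readings kept as valid and D the distance of the dropped reading from m. The section 6.1.1 and Table 3 rule records m. The Table 2 footnote and Table 4 rule records (2m + m + D)/3 = m + D/3. The recorded values therefore differ by D/3, and under the first rule the sign depends on which reading the measurer drops.

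**3. The plan's own sample size, reproduced.** The inputs from section 11.1 are a difference of 5 mmHg, SD 15 mmHg, 90% power and two-sided alpha 0.05.

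- Normal approximation: n per arm = 2 × (1.960 + 1.282)² × 15² / 5² ≈ 189.1, rounded up to 190 (380 in total).
- Two-sample t-test: power is 0.8999 at 190 per arm and 0.9013 at 191, so 191 per arm, or 382, as stated.
- 382 × 1.2 = 458.4, matching 458.

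**4. Illustration of scale.** The protocol gives no figure for measurement bias, so the shift b is an assumption.

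- SE = 15 × √(2/191) = 1.535 mmHg.
- With no true effect, the rejection rate is P(Z > 1.96 − b/SE) + P(Z < −1.96 − b/SE).

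| Assumed b (mmHg) | Share of 5 mmHg | b/SE | Rejection rate |
|---|---|---|---|
| 0 | 0% | 0 | 0.050 |
| 0.5 | 10% | 0.326 | 0.0511 + 0.0111 = 0.062 |
| 1 | 20% | 0.651 | 0.0954 + 0.0045 = 0.100 |
| 2 | 40% | 1.303 | 0.2556 + 0.0006 = 0.256 |

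If all 229 per arm complete, SE = 15 × √(2/229) = 1.402, and the same shifts give 0.065, 0.110 and 0.297. More patients do not dilute a systematic shift. These figures ignore covariate adjustment and the physician or centre random effect in section 11.2.

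**The case against.** The trial is openly pragmatic and non-masked, and section 6.3.2 discloses the MIC's position. The protocol also has real safeguards. The automatic device removes observer reading error. Table 3 fixes 3 to 5 minutes of seated rest, cuff size and position, and the reference limb. Section 12.4 requires full verification of primary-endpoint data, which limits recording bias.

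Most of this stands, and it reduces the concern. It does not remove it. A pragmatic design describes how care is delivered and does not require the measurer to see the Notebook first. Verification against source confirms what was recorded, not the choice of readings behind it.

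A reader might infer several stronger points that the documents do not support:

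- **That the physician who trained a patient takes that patient's reading.** The protocol names no operator. This is possible but not stated.
- **That rest time and technique are left to the operator.** Table 3 sets them. It sits under the selection visit, but its heading covers office measurement generally.
- **That the control Notebook's first-sheet entry for the arm reveals the trial group.** That entry means the limb. The group is revealed by the items found only in the intervention version.
- **That an uninvolved measurer needs no extra staff.** The size of the MIC team is not given, there are 21 centres, and at 24 months the nurses who take over the MIC role also help with plan renewals.

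**Conclusion.** The point holds as a design weakness that can be partly avoided. The primary reading is collected by unblinded staff, group-revealing material may be seen before it is taken, and discretion remains over repeat and valid readings under two differing averaging rules.

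The size of any bias is unknown. It is plausible that it would favour the intervention, but nothing in the protocol shows this. A reader might take the false-positive rates of about 6%, 10% and 26% as estimates for this trial. They are not: they rest on assumed constant shifts of 0.5, 1 and 2 mmHg, SD 15 and 191 completers per arm, and show only that a shift small against the 5 mmHg target would matter.

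Only part of the bias is avoidable, because patients know their own group and masking the measurer does not change that. The change is worth making because it protects the sole primary endpoint and its main elements cost almost nothing.

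**What to change.** Amend sections 6.3.2, 6.5 and 8.5.3 and the blood pressure definition (section 6.1.1, the Table 2 footnote, Table 3 and Table 4):

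1. At the 6-, 12- and 24-month visits, blood pressure is the first procedure and is entered in the CRD before the Patient's Notebook or the treatment record is opened.
2. All device readings are stored or printed and kept as source. One numeric rule states when a third reading is taken and which readings are averaged, so that section 6.1.1 and Table 3 agree with the Table 2 footnote and Table 4. Averaging every reading taken would remove the selection step.
3. Patients are asked not to mention their group until the pressure is entered.
4. Where existing staffing allows, the reading is taken by a team member who did not train, phone or run group sessions for that patient. The protocol states who that is.

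The sample size does not change and no extra visit is needed. Items 1 to 3 are wording and visit order. Item 4 takes some scheduling effort and is conditional because the protocol does not give the team size. Some patients will still disclose their group, and bias from patients knowing it remains.

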## **6.4 Intervention**

### **6.4.1 Intervention group**

The trial intervention is not pharmacological; instead, it involves modifying usual clinical practice. The intervention for self-monitoring and self-adjustment of medication consists of three key elements:

- 1) Patient training: This involves providing information and training on arterial hypertension, its associated risks, its management, the benefits of achieving adequate control, and general measures for improved control.
- 2) Training for self-monitoring: Patients will receive instruction on the correct method for ambulatory blood pressure monitoring (AMPA), as well as guidance on how to measure their blood pressure and record the values using the provided tools.
- 3) Training for self-adjustment: Patients will be educated about target blood pressure goals, individually tailored to each patient. They will also learn how to respond when faced with specific blood pressure readings, including the self-adjustment of their pharmacological treatment.

#### **6.4.2 Control group**

Patients assigned to the control group will receive information about hypertension and the importance of its appropriate management (as outlined in point 1 of the intervention). The control group will not undergo any additional interventions to simulate routine clinical practice management.

#### **6.5 Patients follow-up**

The follow-up of the patients will be conducted by the MEFIs in line with routine clinical practice conditions. MEFIs will be responsible for patient selection and inclusion in the trial and will execute the training actions as outlined in point 6.4.

Additionally, the MIC team will reinforce the training and information actions specified by the MEFI and defined in point 6.4. However, it's important to note that the MIC team will not make clinical decisions or modify the management or recommendations of the MEFI. They will also handle data collection during the scheduled visits in the study, including the baseline visit and follow-up visits at 6 and 12 months, working in collaboration with the MEFI.

In the first 12 months of the study, the MIC team will conduct bi-monthly telephone reinforcement sessions. These sessions aim to contact patients in the intervention group with the goal of improving adherence to the intervention and addressing any potential concerns.

In the second year (passive or pragmatic follow-up), patient follow-up will be aligned as closely as possible with routine management in usual clinical practice. Therefore, the role of the MIC will be carried out by a nurse

#### **6.6 Identification of the data to be recorded**

The MEFIs, in collaboration with the MICs, will be responsible for collecting data at each of the Health Centers during the baseline and follow-up visits. The MICs will work in agreement and in cooperation with the MEFIs. It's important to note that the MICs will not make any clinical decisions regarding the patients participating in the study; this responsibility solely rests with the MEFI.

In cases where, during the baseline or follow-up visits, the MICs obtain additional health-related information from the patients (such as medical history or comorbidities) or acquire more recent study variables than those recorded in the patient's electronic medical record (e.g., BMI, blood pressure), they will include this information in the patient's clinical history. To facilitate this process, a meta-profile will be created (ADAMPA study), ensuring that all patient information (study variables) used in the trial is accurately reflected in the patient's medical record.

The data will be recorded in the visits -baseline, at 6 months, the final at 12 months and the extension at 24 months in the Data Collection Notebook (CDR) prepared for this purpose. The CDR will be completed in computer support. The sources to obtain the necessary data for the study will be:

- The electronic medical record of the Ambulatory Information System –SIA- (ABUCASIS) available in all Health Centers.
- The ORION program that allows access to the electronic hospital medical record.
- The clinical interview with the patient at the established visits (baseline, at 6, 12 and 24 months).
- Information on paper: serious adverse events and self-monitoring and self-adjustment booklet.
- Additional information will be extracted from the Valencia Health System electronic databases: Minimum Basic Data Set (MBDS), ABUCASIS and the Population Information System (SIP).

The following information will be collected at each visit.

Table 2. Data collection throughout the trial

| Visita basal                                                                                                                                                                                                                                                                                                                                      | Visitas 6 y 12 meses                                                                                                                                                                                                                                                   | Visita 24 meses                                                                                                                                                                                                            |
|---------------------------------------------------------------------------------------------------------------------------------------------------------------------------------------------------------------------------------------------------------------------------------------------------------------------------------------------------|------------------------------------------------------------------------------------------------------------------------------------------------------------------------------------------------------------------------------------------------------------------------|----------------------------------------------------------------------------------------------------------------------------------------------------------------------------------------------------------------------------|
| 
 
- BP*
 
- Sociodemographic information
 
- Lifestyle habits**
 
- Comorbidities
 
- Duration of hypertension
 
- Antihypertensive treatments
 
- number of concomitant treatments
 
- Health services use***
 
- Quality of life (EQ5D)
 
 | 
 
- BP*
 
- Lifestyle habits**
 
- Health services use***
 
- Adverse events
 
- Antihypertensive treatments
 
- number of concomitant treatments
 
- Quality of life (EQ5D)
 
 | 
 
- BP*
 
- Lifestyle habits**
 
- Health services use***
 
- Adverse events
 
- Antihypertensive treatments
 
- Quality of life (EQ5D)
 
 |

\*Blood pressure; \*\* Smoking habit, exercise, BMI; \*\*\*Information relative to the previous year. Its determination will be made at the health center with a validated automatic electronic sphygmomanometer. At least 2 measurements will be taken in a seated position, spaced at 1-2 minutes, and another additional measurement if the first 2 are very different. The average of the measurements taken will be recorded (8).

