#### **6.1.2 Secondary outcome measures**

1. Difference in mean systolic blood pressure, in mmHg at 6 and 24 months of follow-up between intervention and control groups determined at physicians' practice with a validated automatic electronic sphygmomanometer.
2. Difference in mean diastolic blood pressure, in mmHg at 6, 12 and 24 months of follow-up between intervention and control groups determined at physicians' practice with a validated automatic electronic sphygmomanometer.
3. Percentage of patients with SBP <140 mmHg and DBP <90 mmHg at 6, 12 and 24 months of follow-up.

4. Quality of life (as measured by EuroQoL-5D) at 6, 12 and 24 months of follow-up.
5. Adherence measured by proportion of days covered (PDC) at 6 and 12 months of follow-up.
6. Persistence, defined as period of continuous use of the corresponding drug from the beginning of the follow-up until its discontinuation at 6 and 12 months of follow-up.
7. Therapeutic inertia (TI), defined as the number of patients whose pharmacological treatment had not been modified, divided by the number of patients not reaching the target values (SBP and/or DBP measurements taken at 6 and 12 months of follow-up), according to the recommendations of the European Society of Hypertension and European Society of Cardiology (19).

Other outcome measures:

1. Changes in lifestyle (smoking, exercise, body weight) at 6, 12, and 24 months compared to these characteristics at baseline.
2. Clinical events: We will assess if any of the following adverse events are present during the follow-up: angina, myocardial infarction, stroke, hypotensive crisis and death.
3. Use of health services for hypertension at 6, 12 and 24 months.
4. Incremental cost per quality-adjusted life year gained in the intervention group compared to the control group.
5. Views and experiences of patients and health professionals on the self-management (SMBP plus self-titration) of hypertension.

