| Differences in changes in lifestyles (smoking, exercise, weight) at 6, 12, and 24 months with respect to the baseline measurement.                            | Changes in lifestyles will be evaluated based on the information collected at follow-up visits.                                                                                                                                                                                                                                                                               |
| Difference between groups in relation to the occurrence of adverse events: angina, myocardial infarction, stroke, hypotensive crisis and death.               | Hospitalizations due to adverse events will be collected at follow-up visits. Outpatient and emergency visits due to hypotensive crises will also be collected.                                                                                                                                                                                                               |
| Differences in the use of health services during follow-up (6, 12 and 24 months).                                                                             | Including HTA-related primary medical and nursing care consultations (at the center by appointment or without an appointment, by telephone and at home). Visits to emergency hospital services, hospital admissions, hospitalization days per admission and main diagnosis                                                                                                    |
| Incremental cost per additional quality-adjusted life year gained in the intervention group compared to the control group.                                    | Cost-consequence analysis and cost-effectiveness analysis                                                                                                                                                                                                                                                                                                                     |

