### Economic analysis

The economic analysis will include a cost-consequence analysis, estimating both the costs (hospitalizations, outpatient visits, emergency visits and antihypertensive drugs) and the potential benefits (e.g. reduced incidence of stroke, myocardial infarction, etc.) in natural units. In addition, we will collect information on Health-Related Quality of Life (HRQOL) through the EQ-5d questionnaire, which will allow us to obtain utilities and therefore perform a cost-utility analysis with the estimated benefits in terms of Quality-Adjusted Life-Years (QALY).

A modeling will be performed to obtain longer-term predictions of the results observed in the trial. The results on which this modeling will be based will be survival, quality of life and costs associated with clinical events. A sensitivity analysis (deterministic and probabilistic) will be performed to analyze the robustness of the results. Key parameters will be modified to determine their impact on results. All analyses will be performed using STATA version 14.

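### The one-year look-back for health-service use reaches back before the trial at the 6-month visit, and the cost list leaves out the intervention's own delivery cost

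*Protocol*

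**What the plan says.** **Look-back.** Table 2 of the Protocol (section 6.6) lists "Health services use" with a triple asterisk in all three visit columns. The 6- and 12-month visits share one column, headed "Visitas 6 y 12 meses". The only note for the triple asterisk is "Information relative to the previous year", with no exception for 6 months. The visit schedule in the same section is: "The data will be recorded in the visits -baseline, at 6 months, the final at 12 months and the extension at 24 months".

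**Outcome.** Section 6.1.2 lists "Use of health services for hypertension at 6, 12 and 24 months" among the other outcome measures. Table 4 (section 9.1) words it as "Differences in the use of health services during follow-up (6, 12 and 24 months".

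**Costs.** The economic analysis in section 11.2 will be done by "estimating both the costs (hospitalizations, outpatient visits, emergency visits and antihypertensive drugs". The bracketed list ends there. The benefits in the same sentence are introduced as examples and left open-ended.

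**Resources given to the intervention arm.** Section 6.5: "In the first 12 months of the study, the MIC team will conduct bi-monthly telephone reinforcement sessions", aimed at intervention patients. Section 6.4.1 describes training in self-monitoring, with tools supplied, and training in self-adjustment. Section 8.5.2 adds training at the baseline visit and periodic group sessions. The control group receives only the general hypertension information (section 6.4.2), and its baseline visit is for data collection alone (section 8.5.2).

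**The concern.** A 12-month window read at a visit 6 months after baseline takes in time when neither arm had received anything. That time cannot show a treatment effect, so it pulls a relative comparison towards no difference, and it is not use during follow-up as Table 4 requires.

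The cost list raises a different problem. The 12-month effect includes whatever the training, calls and group sessions contribute, but the listed costs do not include their price. The omission falls on one arm only and therefore has a known direction. Cost-effectiveness is the third stated objective (section 5.2), and incremental cost per QALY is a named outcome.

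**Working it through.** The plan gives no figure of its own on this point, so there is nothing to reproduce. The check is interval arithmetic on the look-back windows, followed by a comparison of the cost list with the resources described.

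**Inputs.** Visits at 0, 6, 12 and 24 months (section 6.6); 12-month look-back at each (Table 2 note); 229 patients per arm (section 1). Time zero is the baseline visit.

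**Windows as written**

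| Visit | Window (months) | Before baseline | After baseline |
|---|---|---|---|
| Baseline | -12 to 0 | 12 | 0 |
| 6 months | -6 to +6 | 6 | 6 |
| 12 months | 0 to 12 | 0 | 12 |
| 24 months | 12 to 24 | 0 | 12 |

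At 6 months, 6/12 = 50% of the window precedes baseline. It overlaps the baseline window by 6 months and the 12-month window by 6 months. The 12- and 24-month windows do not overlap each other and together cover months 0 to 24 exactly.

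**Dilution at 6 months.** Assume the same constant rate in both arms before baseline, continuing in controls, and a true rate ratio RR in the intervention arm afterwards. Then:

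observed ratio = (6 + 6 x RR) / 12 = (1 + RR) / 2

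- RR 0.80: (6 + 4.8)/12 = 0.90
- RR 1.20: (6 + 7.2)/12 = 1.10
- RR 1.50: (6 + 9)/12 = 1.25

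This holds on the ratio scale, or when the count is read as an annual rate. The absolute difference in mean contacts is unchanged in expectation: at one contact a month in controls, 10.8 - 12 = -1.2, the same as 4.8 - 6 = -1.2. It does carry the added noise of six pre-trial months, and each arm's level is overstated.

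**Delay between randomisation and baseline.** Randomisation takes place at the selection visit, and the baseline visit is arranged afterwards by telephone (section 8.5.1). With a delay of d months, the pre-randomisation share is (6 - d)/12. For an assumed d = 1 this is 5/12 = 42%, so half is a slight upper figure.

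**Windows after the fix.** Counting from the previous visit gives 0-6, 6-12 and 12-24 months: no pre-baseline time, no overlap, 24 months in total.

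**Delivery cost.** Of the resources described for the intervention arm, none of these appears by name among the four listed items: self-monitoring and self-adjustment training, telephone sessions, group sessions, supplied tools. For the calls alone, if bi-monthly means every two months, 229 x 6 = 1,374 are planned over 12 months with all patients retained. If c is the omitted cost per intervention patient, incremental cost is understated by c, and cost per QALY by c divided by the QALY gain (for a positive gain). The documents give neither c nor an expected QALY gain.

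**The case against.** **The correct window is recoverable.** Section 6.6 names electronic primary-care and hospital records and health-system databases as sources. Both arms also receive notebooks with sheets for recording care contacts, issued after randomisation and brought to the 6-month visit (sections 8.5.1 to 8.5.3). Table 4 already refers to follow-up only. This stands to the extent that the fault is easily cured. It does not remove it: the Table 2 note is the only look-back window stated for service use, and nothing says that the records will be cut at baseline. For adverse events, section 10 does count from the previous visit.

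**The footnote may be careless drafting.** Blood-pressure measurement text follows directly after it. That is a fair reason to doubt intent, but the mark and its note match, and the conflict with Table 4 at 6 months is literal.

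**Detailed costing is often left to a later plan.** True, and silence alone would be no finding. Here the Protocol gives a list with no sign that it is partial, beside a list of benefits that is openly partial. Nothing in section 11.2 excludes delivery cost, so the criticism applies to the list if it is followed as written.

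**Stronger readings that the documents do not support**

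- *Months 0-6 are counted twice.* A reader might infer this from the overlap. No rule adds the 6- and 12-month reports. If they were added, 24 months would be counted for 12, and a constant arm difference would count as 6 + 12 = 18 months instead of 12 (1.5 times). That is a risk only.
- *All the cost inputs are wrong.* The 12- and 24-month reports give correct service use for months 0 to 24.
- *Notebooks and visits after self-adjustment are further omitted costs.* Notebooks go to both arms, and those physician visits may already count as outpatient visits.
- *The bias can be put in euros per QALY.* Any such figure would rest wholly on assumed inputs.

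**Conclusion.** Both parts hold, within limits.

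1. The look-back is wrong at the 6-month visit only. About half of that window, slightly less if baseline lags randomisation, precedes the trial and contradicts Table 4. On the ratio scale the effect is pulled about halfway to 1 (0.80 becomes 0.90), assuming equal and constant prior rates.
2. The cost list, followed as written, leaves out delivery resources borne only by the intervention arm. The direction of bias is clear: incremental cost is understated and cost per QALY looks better than it is. Its size cannot be derived from the documents.

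The primary outcome is untouched. Service use and cost per QALY are classed as tertiary in Table 4, which limits the weight of the point. It should still be corrected, because cost-effectiveness is a stated objective and the correction is cheap.

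**What to change.** - In the Table 2 note, keep the previous-year window for the baseline visit only. At 6, 12 and 24 months, record use *since the previous study visit*, taken by date from the electronic records that section 6.6 already names. State that the 12- and 24-month totals are built from these non-overlapping periods.
- In the section 11.2 cost list, add intervention delivery: self-monitoring and self-adjustment training time, telephone sessions, group sessions and the tools supplied. Report the incremental cost-effectiveness ratio with these included. Table 2 has no item for these resources, so they need to be logged as they are used.
- Do not add the notebooks, which both arms receive, or physician visits after self-adjustment that are already counted as outpatient visits.

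The cost is one footnote, one extra cost line, a little more costing work and probably a slightly less favourable ratio. Visits, sample size and the primary analysis do not change.
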